#### Economic Analysis

Cost-effectiveness analysis (Drummond, 2015) from a health service perspective will be employed. As the intervention is planned to be delivered within a 12-month timeframe, discounting will not be used. Sensitivity analysis will investigate the major potential factors that may influence cost-effectiveness including variation in intervention effectiveness, adherence to OPC, dosage associated with effectiveness, and variation in intervention costs, particularly staff input and travel costs. Health service costs will include therapist training, intervention, and travel time and will exclude lost productivity and time costs of family members. Health effectiveness will be based on COPM (MCID ≥ 2 points). As therapists will be recruited throughout the North and South Islands, the study design is expected to provide information regarding national transferability.

### Analysis Population

All dyads who formally consent to participate, and complete at least one intervention session, will be included in the analysis as the “as randomized population.” This population is the primary analysis population for all analyzes.

A subset of the population who meet all inclusion and exclusion criteria and have completed one or more sessions with a therapist enrolled in the study will be included in the per-protocol population. All decisions on participant exclusions from the per-protocol population will be made prior to database closure and will be justified in the clinical study report.

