### Randomization Process

Therapists represent clusters in the study design with study participants defined as caregivers and their children with ND (dyads). After completion of a retrospective case note audit, therapists (N ≥ 14) will be randomized into the OPC or Usual Care groups via a computer-generated randomization sequence, stratified by service (Harris et al., 2009). Thus, services with multiple therapists enlisted in the study will have a mixture of control and intervention group therapists. Therapists in both groups will then each recruit child–caregiver dyads to the study from successive eligible referrals to the service until the total sample size (N = 84) is reached. To enable adequate recruitment of Māori dyads for equal explanatory power for ethnicity, therapists will continue to invite Māori to participate until 42 Māori dyads are recruited (potentially increasing the total sample size to N = 126), or data collection has ended.

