### Sample Size

The Minimal Clinically Meaningful Difference (MCID) on the COPM is indicated by a change in occupational performance scores of two points on a 10-point scale (Law et al., 2014). A minimum sample size of 46 dyads is required to detect the MCID with 90% power at a two-sided alpha of 0.05, assuming a population standard deviation in COPM scores of two points (Graham et al., 2013). For an ANCOVA analysis of a cluster RCT, this sample size must be multiplied by a design effect to account for the correlation structure of the data (Rutterford et al., 2015). The final sample size has thus been inflated to 84 dyads (spread evenly between 14 or more therapists) to account for clustering (design effect = 1.2), treatment contamination in the control group (20%), and participants lost-to-follow-up (15%). We seek to recruit a minimum of 42 dyads where the caregiver is of Māori ethnicity, to allow for an adequately powered subgroup analysis with 80% power to detect a difference in treatment effect on the COPM.

For post-intervention interviews, 10 Māori who have received a minimum of one high-fidelity OPC session will be successively invited to participate. This sample size is based on prior research (Walker et al., 2017) and will be adjusted according to information power (Braun & Clarke, 2022; Malterud et al., 2016).

In relation to blinding: First, a research fellow (RF), blinded to group allocation, will collect all outcome measures in both intervention and control groups. The RF will have no contact with therapists or access to study data about therapists. Second, dyads will be blind to group allocation. Therapists will not be blinded to group allocation but will be requested not to refer to their group allocation or OPC by name to caregivers and children. Third, the biostatistician will not be blinded however the statistical analysis plan and statistical analysis code will be prepared a priori to the collection of the 16-week outcome data to ensure that analysis processes are not influenced by the data collected.

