## Measures and Procedures

### Outcome Measures

#### Primary Outcome Measure

The primary outcome is children's participation in personally valued life situations, measured 16 weeks after the first recorded therapy session using the COPM (Law et al., 2014). The mean between-group difference will be calculated by adjusting for values at recruitment (T1, see Figure 1). All caregivers, and children with cognitive and communication skills at or above age 8, will be invited to identify up to five life situations which are important to them, allowing formulation of future-oriented participatory goal statements. Consistent with COPM guidelines, caregivers and children will rate current “performance” and then ‘satisfaction with performance’ on 10-point Likert scales. The “performance” scale is the primary outcome.

The COPM has robust psychometric properties with paediatric ND populations, and is widely considered to be a gold standard measure of individualized performance in areas of personal value (Cusick et al., 2006, 2007; Law et al., 2014) and participation (Sakzewski et al., 2007).

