## Statistical Methods

Participant data will be analyzed as-randomized (intention-to-treat, ITT). Two-sided *P* values will be reported and an alpha of 0.05 used for the construction of confidence intervals and for determining statistical significance. The analysis will be performed using R specialist statistical software (R Core Team, 2021). A detailed statistical analysis plan (SAP) will be prepared by the study biostatistician and agreed upon by the PI prior to any analysis of the data.

Differences between groups in outcome measures (COPM scores, DASS-21, and PEDI-CAT scores at 16 weeks) will be estimated with 95% confidence intervals using a “constrained baseline analysis” where a linear mixed-effects model is fitted to the individual level data with time and treatment included as fixed effects. Correlations within the data will be accounted for by incorporating the following random effects; cluster, an individual within cluster, and time within cluster, and a Kenward–Roger correction will be applied due to the small number of clusters (Hooper et al., 2018). Psychometric analysis of therapist self-completed and researcher-completed OPC-FM scores will be conducted to assess the validity and reliability of this instrument. Researcher completed OPC-FM scores, Session Characteristics, and SRSs will be summarised first by a therapist, and then by the treatment group. Linear regression analysis adjusting for clustering will be used to estimate mean treatment group differences with 95% confidence intervals.

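### The population called as-randomized (ITT) requires a completed session, so it is a modified-ITT set, and no analysis in the article includes dyads who never start

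*Protocol article*

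**What the plan says.** - **Principle (Statistical Methods).** "Participant data will be analyzed as-randomized (intention-to-treat, ITT"). Additional Analyzes also refers to the whole ITT population.
- **Primary set (Analysis Population).** "All dyads who formally consent to participate, and complete at least one intervention session, will be included in the analysis", under the name as-randomized population. Its role: "This population is the primary analysis population for all analyzes".
- **Per-protocol set (same section).** Dyads who meet all eligibility criteria and "have completed one or more sessions with a therapist enrolled in the study will be included in the per-protocol population".
- **Timing of the primary outcome (Primary Outcome Measure).** COPM performance, "measured 16 weeks after the first recorded therapy session using the COPM", adjusted for the value at recruitment (T1).
- **Order of events (Randomization Process).** Therapists are randomized first. "Therapists in both groups will then each recruit child–caregiver dyads to the study from successive eligible referrals".
- **Blinding (last paragraph of Sample Size).** "Therapists will not be blinded to group allocation". Dyads and the outcome assessor are blinded.
- **Missing Data.** The primary analysis is a likelihood-based mixed model on all collected data. A sensitivity analysis assumes no improvement where the outcome is missing.

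**The concern.** An intention-to-treat set should not depend on whether treatment was received. Here a consented dyad enters the primary analysis only after a session has been completed. That event comes after the therapist was randomized and depends partly on how an unblinded therapist schedules and engages the family. If the number or prognosis of non-starters differs by arm, the primary comparison shifts, and the article describes no analysis that would show it.

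The trial is presented as a test of effectiveness in ordinary service delivery, where failure to start is part of the effect of interest. The restriction also reaches the other analyses, because the same set is primary for all of them.

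**Working it through.** **1. The plan's own figures.** The plan assumes a difference of 2, SD 2, two-sided alpha 0.05 and 90% power. The t-test calculation gives 22.02 per arm, rounded up to 23, so 46 dyads. Inflating: 46 × 1.2 / 0.80 / 0.85 = 81.2, so 82, and 14 therapists × 6 dyads = 84. Both stated figures reproduce. The point concerns a definition and disputes neither number.

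**2. The sets side by side.**

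| Set | Consent | At least one session | Eligibility confirmed | Dose or fidelity |
|---|---|---|---|---|
| ITT as usually understood | yes | no | no | no |
| Primary set as defined | yes | yes | no | no |
| Per-protocol set | yes | yes, with an enrolled therapist | yes | no |

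The primary set differs from ITT by the session condition. The per-protocol set differs from the primary set essentially by eligibility. How many dyads that removes is not stated.

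**3. Can a non-starter enter anywhere?**
- The 16-week COPM is counted from the first recorded session, so a dyad without one has no defined assessment date.
- Analysis Population removes the dyad before the mixed model or the no-improvement analysis is applied.
- The as-treated analysis in Additional Analyzes classifies dyads by fidelity ratings of sessions, which a non-starter does not have.

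So no analysis in the article covers them.

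**4. The boundary is loosely drawn.** OPC Dosage defines a session as at least 30 minutes but also says OPC sessions can last from 20 minutes. Analysis Population does not say what an intervention session is under usual care. These passages need reconciling, because membership of the primary set rests on the term.

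**5. Size (assumed rates; the article gives none).** Let p be the proportion not starting in an arm, and let gap be how much worse non-starters do than starters in that arm. Then

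mean among starters = mean of all dyads + p × gap,

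and, with the same gap in both arms,

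shift in the difference = (p₁ − p₂) × gap.

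With 10% v 3% and a gap of 1 to 2 points: 0.07 × 1 = 0.07 to 0.07 × 2 = 0.14. The sign depends on which arm has more non-starters: if OPC has more, the starters-only analysis flatters OPC. Relative to the 2-point difference, this is 3.5% to 7%.

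For scale, 84 × 0.85 = 71.4 dyads, or 35.7 per arm, gives an unadjusted standard error of √(1.2 × 2² × 2/35.7) = 0.52. The shift is therefore about 0.13 to 0.27 standard errors.

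**6. A harsher scenario.** Assume a 2-point difference among starters, no change at all in non-starters, and a usual-care mean change m of 1 or 2 among starters. The all-dyad difference is (m + 2)(1 − p_OPC) − m(1 − p_UC).

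| Not starting, OPC v usual care | m = 1 | m = 2 |
|---|---|---|
| 10% v 10% | 1.8 | 1.8 |
| 15% v 5% | 1.6 | 1.5 |
| 5% v 15% | 2.0 | 2.1 |

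The balanced row already falls to 1.8. Part of the change in the 15% v 5% row is therefore dilution from a different estimand, not selection bias. At 5% to 20% non-starting overall, about 4 to 17 of 84 dyads would be left out.

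**The case against.** The strongest reply has five parts.

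- **A recognised set, openly stated.** Requiring one session is a known modified-ITT rule. This stands, and it makes the label the main fault. The label still matters, because the article claims ITT twice.
- **Differential non-starting is not shown.** Dyads are blind to allocation, therapists are asked not to name OPC or their group, and before the first session a caregiver has had no coaching to react to. This largely stands. Scheduling by unblinded therapists remains a route.
- **Consent and T1 also follow randomization.** A reader might infer that the session rule is what costs the trial the protection of randomization, and that dropping the rule restores it. The document does not support that: recruitment by unblinded therapists is open to the same influence. Dropping the rule removes one later source of selection and no more.
- **Baseline-only data help little.** A reader might suppose the mixed model can use non-starters' T1 scores and solve the problem at no cost. In the constrained baseline model such dyads inform the common baseline mean and add almost nothing to the 16-week contrast. The gain comes from obtaining their follow-up COPM, which needs a new anchor date.
- **Receipt of OPC is examined elsewhere.** The as-treated analysis requires two of three fidelity assessments at 80% or above. It is tempting to call the per-protocol analysis an uninformative repeat, but that goes too far. It also requires an enrolled therapist and confirmed eligibility, and the overlap of the two sets is unknown.

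**Conclusion.** The contradiction is real and concerns the primary population: the article declares ITT and defines modified ITT, conditional on an event after randomization. No described analysis covers non-starters, and the no-improvement sensitivity analysis does not reach them.

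The size of any bias cannot be derived from the document. Under 3% v 10% non-starting and a gap of 1 to 2 points it is 0.07 to 0.14 COPM points, probably small. The larger movements in the harsher scenario need a 15% v 5% imbalance and no change in non-starters, and they mix dilution with bias. A reader might infer that the primary result is materially biased; nothing in the article shows that. The passage is wrong as written and worth correcting, but this is not a flaw that by itself threatens the trial's conclusion.

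**What to change.** **Preferred change**
1. Define the as-randomized population as all consented dyads, analysed by their therapist's allocation whether or not a session took place.
2. For dyads with no session, seek the COPM 16 weeks after T1 or after the planned first-session date. If it is not obtained, include them in the no-improvement sensitivity analysis.
3. Report the number of non-starters by arm.
4. Keep the one-session rule for the per-protocol set only, and state what counts as a session in each arm.

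**Minimum, if the current set stays primary:** label it modified ITT, report non-starters by arm, and add a sensitivity analysis on all consented dyads.

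**Cost.** Wording in the protocol and analysis plan, a new follow-up anchor, and a few extra contacts by the blinded research fellow. The target of 84 does not change. The estimate may be slightly diluted: with 10% non-starting in both arms and no difference among non-starters, 2.0 becomes 2 × 0.9 = 1.8. The definition should be settled before outcome data are analysed.

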### Missing Data

The presence of missing data in this cluster RCT will be handled as recommended by Fiero et al. (2016). Firstly, all efforts will be made to optimize collection of the primary measure (COPM). Secondly, a likelihood-based mixed model including all collected data will be used for the primary analysis. Mixed models provide the greatest power and are valid for cases where data is missing at random (MAR). Finally, a sensitivity analysis will be performed where subjects’ missing outcome data will be assumed to have not improved at all during the study.

## Discussion

This RCT protocol outlines a significant step on the continuum of translational research (Vukotich, 2016), building on previous efficacy and feasibility studies to evaluate its effectiveness in the service delivery contexts it is intended for. Studies embedded in real-world contexts are needed to understand and address the factors that contribute to the science-implementation gap (Olswang & Prelock, 2015) for OPC. Subsequent studies examining the scalability of OPC implementation can then be planned. Distinctively, this study incorporates multiple strategies to report and monitor intervention fidelity and the nature of usual care as a comparison group. This study provides transparency to usual care in relation to therapist inputs, health outcomes, and economic impacts. This study also illustrates translational research for complex interventions (Murray et al., 2010) situated in the occupational therapy and rehabilitation fields.

With the recruitment of the intended sample size, important secondary analyzes will be possible exploring the effectiveness of OPC for Māori and how OPC was experienced by Māori caregivers. Internationally, these analyzes with Māori extend our understanding of the relationship between culture and responsive occupational therapy interventions.

### Limitations

This study may be limited by recruitment of the target sample size of child–caregiver dyads given the Aotearoa/New Zealand population size and the ongoing effects of COVID-19 on participating services. COVID-19 may also affect service delivery patterns in a range of ways that do not provide an accurate representation of the usual service delivery context, however, this will be balanced for both OPC and Usual Care groups. The known high variability of usual care as a comparison may reduce the certainty of findings and challenge the pooling of data in future meta-analyzes of OPC research. The established known therapeutic effects of goal setting (Graham et al., 2013; Locke & Latham, 2002) are an unavoidable limitation of using goal setting and individualized goal progress as the primary outcome. This may have the effect of diminishing the change observed in the OPC group relative to the Usual Care group, producing a conservative assessment of the treatment effect. Therapists from the same agencies may be randomized to either group, introducing a risk of contamination. This was a necessary risk in order to achieve the study sample size, and strategies were put in place to minimize contamination within sites. Contamination will be identified through analysis of the retrospective case note audit and OPC-FM findings.

## Conclusions

The proposed study will determine the effectiveness of OPC to improve the occupational performance and participation of children with ND and their families when implemented in existing service delivery contexts. Findings will inform future strategies to reduce the science-implementation gap for OPC.

## Key Messages

OPC is a transdisciplinary intervention conceptually grounded in occupational therapy theory, and coaching-related principles of autonomy, self-determination, and behaviour change.OPC has evidence of effect under controlled conditions but translational research studies, situated in service delivery contexts, are now needed.This study protocol enhances the scholarship of occupational therapy research through providing transparency of a planned RCT of the effectiveness of OPC.

